**Figure 1 fig1:**
[figure not shown]
Study design flowchart: a detailed depiction of participant progression through each stage of the study.

The primary outcome is pain intensity, assessed using the VAS, a widely recognized and validated tool. VAS scores will be recorded at baseline, at 2 and 4 weeks during treatment, and again at a 1-month follow-up after completion of the intervention. Secondary outcomes assess shoulder joint function across four domains. First, ROM will be measured to evaluate mobility of the affected shoulder. Second, the absolute vertical distance difference between the medial superior angle of the scapula on the affected side and the second thoracic spinous process will be recorded. Third, musculoskeletal ultrasound will be used to assess five key indicators: presence of effusion around the long head of the biceps tendon sheath, calcification in the supraspinatus muscle, calcification at the insertion of the subscapularis tendon, subdeltoid bursa thickness (in millimeters), and the distance from the acromion to the greater tuberosity of the humerus. Lastly, the MBI will be used to evaluate overall independence in daily living activities. Covariates include age, sex, body mass index (BMI), stroke type (hemorrhagic or ischemic), and time since stroke onset. All outcome measures will be collected at baseline, 2 weeks, and 4 weeks after treatment begins. A follow-up VAS will be conducted 1 month post-intervention to assess the sustained effects of DPS in relieving post-stroke shoulder pain. The physical function assessments will be performed by trained evaluators blinded to treatment allocation, and data analysis will be conducted by statisticians also blinded to group assignments.

Detailed outcome variables and their classification as endpoints or intermediate measures are summarized in Table 1.

**Table 1 tab1:** Baseline assessment and sequence of trial measurements for primary and secondary outcomes.

	Before-intervention	Mid-intervention	Post-intervention	1-month follow-up
Time (weeks)	**0**	**2**	**4**	**8**
Baseline				
Sex (male/female)	**√**			
Type of stroke (ischemia/hemorrhage)	**√**			
Age, y	**√**			
BMI	**√**			
Time since stroke, y	**√**			
Primary outcome variable				
VAS	**√**	**√**	**√**	**√**
Secondary outcome variables				
Shoulder ROM				
Flexion (0–180°)	**√**	**√**	**√**	
Extension (0–50°)	**√**	**√**	**√**	
Abduction (0–180°)	**√**	**√**	**√**	
Adduction (0–40°)	**√**	**√**	**√**	

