Internal rotation (0–70°)	**√**	**√**	**√**	
External rotation (0–90°)	**√**	**√**	**√**	
Horizontal abduction (0–45°)	**√**	**√**	**√**	
Horizontal adduction (0–135°)	**√**	**√**	**√**	
Absolute vertical distance difference: medial	**√**	**√**	**√**	
Superior scapula to T2 on affected side				
Musculoskeletal ultrasound				
Distance from the acromion to the greater tuberosity of the humerus	**√**	**√**	**√**	
Effusion of the long head of the biceps tendon	**√**	**√**	**√**	
Calcification of the supraspinatus muscle	**√**	**√**	**√**	
Calcification of the subscapularis muscle	**√**	**√**	**√**	
Thickness of the subdeltoid bursa	**√**	**√**	**√**	
Modified Barthel Index	**√**	**√**	**√**	

“√” Indicates that the corresponding outcome will be assessed at that time point.

The study will take place in the Rehabilitation Department of Fuyong People’s Hospital, Bao’an District, Shenzhen, Guangdong Province, China. Ethical approval was granted by the Institutional Review Board of Fuyong People’s Hospital, Bao’an District, Shenzhen.

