### Data analysis

Statistical analyzes will be performed using SPSS version 27.0. All continuous variables will be tested for normality using the Shapiro–Wilk test. Normally distributed data will be expressed as mean ± standard deviation and analyzed using independent sample *t*-tests for between-group comparisons and repeated measures ANOVA for within-group comparisons across time points (baseline, week 2, week 4, and 1-month follow-up). Non-normally distributed data will be reported as medians with interquartile ranges and assessed using the Mann–Whitney U test and Friedman test, respectively. Categorical variables such as gender or stroke type will be analyzed using chi-square tests or Fisher’s exact tests when appropriate. A two-sided *p*-value < 0.05 will be considered statistically significant for all analyzes.

For musculoskeletal ultrasound outcomes, four key indicators will be analyzed: (1) distance from the acromion to the greater tuberosity of the humerus and (2) thickness of the subdeltoid bursa will be treated as continuous variables and analyzed using the same approach as other quantitative measures—independent *t*-tests or Mann–Whitney U tests for between-group comparisons, and repeated measures ANOVA or Friedman tests for within-group changes. (3) Calcifications in the supraspinatus tendon and (4) effusion around the long head of the biceps tendon sheath will be treated as binary variables (presence/absence) and compared between groups using chi-square tests. All ultrasound images will be independently reviewed by two experienced sonographers blinded to group allocation. Inter-rater reliability will be evaluated using Cohen’s kappa for categorical variables and intraclass correlation coefficients (ICC) for continuous variables. Any discrepancies will be resolved by consensus discussion.

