#### Musculoskeletal ultrasound

Musculoskeletal ultrasound is a practical and noninvasive method for detecting structural abnormalities commonly associated with PSSP. Key indicators include the distance from the acromion to the greater tuberosity of the humerus (Figure 9), effusion around the long head of the biceps tendon sheath (Figure 10), calcification in the supraspinatus (Figure 11) and subscapularis tendons, and increased thickness of the subdeltoid bursa (Figure 12). Effusion around the biceps tendon sheath often reflects inflammation or tendinopathy, which can contribute to pain and limited mobility. Calcifications in the supraspinatus and subscapularis tendons are typically associated with chronic rotator cuff conditions that result in impingement and reduced range of motion. Thickening of the subdeltoid bursa is suggestive of bursitis, a frequent source of discomfort in PSSP patients (21).

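### Five ultrasound indicators are declared and scheduled but only four are listed for analysis: subscapularis calcification has none, and the binary indicators make no use of baseline status

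*Protocol article*

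**What the plan says.** All places are in the protocol article.

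- **Study design overview:** "musculoskeletal ultrasound will be used to assess five key indicators". The list that follows includes "calcification at the insertion of the subscapularis tendon".
- **Table 1:** the row "Calcification of the subscapularis muscle" is ticked before, midway through and after the intervention (weeks 0, 2 and 4). No ultrasound item is ticked at the 1-month follow-up.
- **Secondary outcomes, Musculoskeletal ultrasound:** the key indicators are listed again, and the calcification item covers the supraspinatus "and subscapularis tendons, and increased thickness of the subdeltoid bursa". The same section describes how the subscapularis tendon is to be scanned.
- **Data analysis:** for the ultrasound outcomes, "four key indicators will be analyzed". The numbered items are acromion-to-tuberosity distance, bursa thickness, supraspinatus calcification and biceps sheath effusion. The last two "will be treated as binary variables (presence/absence) and compared between groups using chi-square tests". The two continuous indicators also get a within-group analysis over time; the binary ones do not.
- **Data analysis, general rule:** categorical variables, with sex and stroke type as examples, "will be analyzed using chi-square tests or Fisher’s exact tests when appropriate".

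**The concern.** A counted and numbered list of analyses conflicts with a counted list of outcomes in the same article. An analyst who follows the Data analysis section would leave subscapularis calcification unanalysed although it is scanned three times per patient. The Discussion presents ultrasound as the trial's notable innovation, so a gap in that domain will be noticed, and it leaves open after the fact whether the item is reported.

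The second matter is how the binary items are compared. The Discussion wants to read a reduction in effusion as a sign that inflammation has reversed. That is a statement about change within patients. A comparison of presence alone counts a shoulder that never had an effusion in the same way as one whose effusion cleared.

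**Working it through.** **1. Count of indicators**

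| Indicator | Overview | Table 1 | Ultrasound section | Data analysis |
|---|---|---|---|---|
| Acromion-to-tuberosity distance | yes | yes | yes | yes |
| Bursa thickness | yes | yes | yes | yes |
| Biceps sheath effusion | yes | yes | yes | yes |
| Supraspinatus calcification | yes | yes | yes | yes |
| Subscapularis calcification | yes | yes | yes | **no** |

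That is 5 declared − 4 analysed = 1 without an analysis. Table 1 says muscle where the overview says tendon insertion, but it names both calcification items by muscle, so this is loose naming and not a different indicator. After correction there are 2 continuous and 3 binary indicators.

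**2. Arm sizes used below**

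The plan's sample size follows from its inputs (d = 0.91, two-sided α 0.05, power 0.80): 2 × (1.960 + 0.842)² / 0.91² = 18.96, so 19 per arm and 38 in total. Then 38 / (1 − 0.20) = 47.5, so 48, or 24 per arm. These figures only set the arm sizes; the point does not depend on them.

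**3. What ignoring baseline status costs (illustration)**

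The documents give no prevalence or resolution rates. Assumed: baseline prevalence 30%, 50% or 70%; resolution 20% in one arm and 60% in the other; new findings 2% in both.

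At 50% prevalence, expected presence at the end is 0.5 × 0.80 + 0.5 × 0.02 = 41% against 0.5 × 0.40 + 0.5 × 0.02 = 21%, a gap of 20 points. Among those positive at baseline the gap is 80% − 40% = 40 points. The plain comparison dilutes it.

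Two tests were simulated, 8,000 runs per setting:
- Pearson chi-square: N(ad − bc)² / (n²·m·(N − m)), with a, b, c, d the cells of the 2×2 table, n the arm size, N = 2n and m the number positive.
- Mantel–Haenszel, stratified by baseline presence: [Σ(a − n₁m/t)]² / Σ[n₁n₂m(t − m) / (t²(t − 1))], summed over the two strata, where t is the stratum size and n₁ and n₂ are its arm sizes.

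| Per arm | Baseline prevalence | Chi-square power | Stratified power | Gain (points) |
|---|---|---|---|---|
| 24 | 30% | 19.1% | 28.0% | 9 |
| 24 | 50% | 33.0% | 49.1% | 16 |
| 24 | 70% | 53.5% | 66.5% | 13 |
| 19 | 30% | 15.5% | 23.2% | 8 |
| 19 | 50% | 28.1% | 39.8% | 12 |
| 19 | 70% | 44.9% | 56.4% | 12 |

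With no treatment effect (resolution 20% in both arms) the chi-square test rejects in 5.1% to 5.8% of runs and the stratified test in 2.9% to 4.9%. The loss is in power, not validity.

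**4. Small counts**

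Exact enumeration of the type I error of the two tests at nominal 5%, by assumed prevalence:

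| Per arm | Test | 10% | 20% | 30% |
|---|---|---|---|---|
| 19 | Chi-square | 3.6% | 4.9% | 5.3% |
| 19 | Fisher's exact | 1.1% | 2.2% | 2.4% |
| 24 | Chi-square | 4.7% | 5.4% | 5.2% |

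The chi-square test is not materially above 5% in any of these settings.

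**The case against.** The best defence of the omission is that the general rule for categorical variables could cover a fifth indicator, since its examples are not exhaustive. That does not remove the conflict. The ultrasound paragraph sets out separately what is analysed, counts it and numbers it, and this item is missing. It is fair to add that the omission touches one item within one of four secondary domains and leaves the primary outcome alone.

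On the binary comparison more of the defence stands. Baseline adjustment of a secondary item is often left to the analysis plan, which is not shown, so this part is an improvement and not an error. The Abstract also places the secondary outcomes at 4 weeks, which suggests the intended time point although the Data analysis section does not state it.

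Four stronger readings are tempting, and the documents do not support them:

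- **That the test is made at follow-up.** Follow-up in this protocol means the 1-month visit, where only the VAS is taken. The ultrasound comparison can only be at week 2 or week 4.
- **That the test would present baseline imbalance as a treatment effect.** Under randomisation a chance imbalance is part of the error that α already bounds, as the null results above show.
- **That sparse tables make chi-square unsafe.** Expected counts below 5 break a rule of thumb, but the error rates above show no harm, and Fisher's exact test would only be more conservative. The general rule may allow Fisher's test here in any case.
- **That the omission is deliberate selective reporting.** The text says nothing about withholding the item; a drafting slip explains it equally well.

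**Conclusion.** The five-against-four contradiction holds in full and rests on the text alone: subscapularis calcification is declared, scheduled at three visits and given a scanning procedure, and it has no place in the listed analyses. One of five ultrasound indicators is affected. This is wrong as written.

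The baseline point holds as a free improvement. The planned chi-square is valid but discards information already collected, and it does not support the reading of effusion that the Discussion has in mind. The gain of about 8 to 16 points depends wholly on the assumed prevalence and resolution rates. If a finding does not change in 4 weeks, the plain test repeats the baseline comparison, and a stratified test has no variation within strata and says nothing about the arms.

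**What to change.** 1. **Correct the list.** In Data analysis, change four to five and add subscapularis calcification as a third binary indicator, under the same name as in the overview and Table 1.
2. **Fix the comparison.** Name week 4 as the time point for the binary indicators and account for baseline presence, for example with a test stratified by baseline status.
3. **Report resolution of effusion.** Among patients with effusion at baseline, give the number and proportion resolved by arm, as a descriptive result only. At an assumed prevalence of 10% to 20% with 19 per arm this is 19 × 0.10 = 1.9 to 19 × 0.20 = 3.8 patients per arm, too few for a test.

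The cost is a few lines of protocol or analysis-plan text, best settled before the group codes are opened. All the data are already scheduled, and the sample size and visits stay as they are.

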## Assessment of outcomes

The primary outcome of this trial is pain intensity measured by the VAS. Secondary outcomes include shoulder range of motion, scapular alignment (vertical distance to T2), musculoskeletal ultrasound findings, and MBI. A detailed summary of these outcome measures and assessment time points is provided in Table 2.

**Table 2 tab2:** Overview of outcome measures and assessment time points.

Outcome category	Tool/method	Time points	DPS/SCTT groups
Primary outcome	VAS	Baseline, Week 2, Week 4, Follow-up	√/√
Secondary outcomes	ROM of the shoulder joint	Baseline, Week 2, Week 4	√/√
	Vertical distance (scapula–T2)	Baseline, Week 2, Week 4	√/√
	Musculoskeletal ultrasound	Baseline, Week 2, Week 4	√/√
	MBI	Baseline, Week 2, Week 4	√/√

### Primary outcome

The primary outcome of this study is the change in VAS scores from baseline to 2 weeks, 4 weeks after the intervention, and at the 1-month follow-up. The VAS is a widely used and validated instrument for assessing subjective pain intensity. It consists of a 10 cm (100 mm) continuous line anchored by “no pain” at 0 and “worst imaginable pain” at 10 (18). Patients are instructed to mark the point on the line that best represents their current level of pain. The score is determined by measuring the distance in millimeters from the “no pain” anchor to the patient’s mark. The VAS is known for its sensitivity to changes in pain perception and is commonly used in clinical trials to evaluate the effectiveness of interventions. In this study, it functions as a key indicator of symptom change, providing a measurable outcome for assessing the degree of pain relief in patients with post-stroke shoulder pain (19).

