**Methods/design:**

This is a single-center, 4-week randomized controlled trial carried out at the Department of Rehabilitation, Fuyong People’s Hospital, Bao’an District, Shenzhen, Guangdong Province. The objective is to assess the comparative effectiveness of DPS and SCTT in patients with PSSP. Eligible participants are stroke survivors aged between 40 and 60 years who meet the diagnostic criteria for PSSP established in China. Participants will be randomly assigned to one of two treatment groups, receiving one 40 min session each weekday (Monday through Friday) for four consecutive weeks, with rest on weekends. The primary outcome is the change in pain intensity measured by the Visual Analog Scale (VAS) at 2 weeks, 4 weeks, and at a 1-month follow-up. Secondary outcomes include shoulder joint function and general functional recovery at 4 weeks, evaluated using shoulder range of motion (ROM), the absolute difference in vertical distance between the medial superior angle of the scapula and the second thoracic spinous process, musculoskeletal ultrasound findings, and the Modified Barthel Index (MBI).

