### Sample size calculation

This study draws on findings from a previously published clinical observational trial on the application of DPS for post-stroke shoulder pain (15). Sample size estimation was performed using G*Power 3.1 software. The significance level (*α*) was set at 0.05, *β* at 0.20, and statistical power (1−β) at 0.80. Based on the method for comparing two groups of equal size and using an effect size (Cohen’s d = 0.91) as reported in the referenced study, the minimum required number of participants was calculated to be 19 per group, totaling 38. To account for an expected dropout rate of 20%, the sample size was increased to 48 participants. This adjustment ensures sufficient statistical reliability and helps maintain the study’s validity despite potential participant attrition.

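### VAS change at week 2, week 4 and the 1-month follow-up is all primary, each visit is tested at an unadjusted 0.05, and nothing says which result decides the trial

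*Protocol article*

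**What the plan says.** All references are to the protocol article.

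- **Primary outcome:** it is the "change in VAS scores from baseline to 2 weeks, 4 weeks after the intervention, and at the 1-month follow-up". The abstract (Methods/design) agrees: pain is "measured by the Visual Analog Scale (VAS) at 2 weeks, 4 weeks, and at a 1-month follow-up". Table 2 under Assessment of outcomes lists the VAS at "Baseline, Week 2, Week 4, Follow-up". Table 1 places these visits at weeks 0, 2, 4 and 8.
- **Between-arm test (Data analysis):** normally distributed outcomes are "analyzed using independent sample *t*-tests for between-group comparisons", with Mann–Whitney U as the fallback.
- **Repeated-measures methods (Data analysis):** the plan uses "repeated measures ANOVA for within-group comparisons across time points", with Friedman as the fallback. These methods describe change within an arm and do not compare arms over time.
- **Threshold (Data analysis):** a "two-sided *p*-value < 0.05 will be considered statistically significant for all analyzes".
- **Sample size calculation:** alpha "was set at 0.05", power is 0.80 and Cohen's d is 0.91 for two equal groups. The result is 19 per group, 38 in all, raised to 48 for 20% dropout. The visit to which d refers is not stated.
- **Hypothesis (Introduction):** DPS will be more efficacious than SCTT.

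**The concern.** The hypothesis is a superiority claim, so the trial needs one rule for turning VAS results into a yes or no. The article gives three between-arm comparisons equal standing, no single between-arm test that spans them, and the full 0.05 for each. A report could follow this text to the letter and rest its conclusion on whichever visit fell below 0.05. The 5% level assumed in the sample size would then not hold for the main claim, and the stated 80% power would belong to no identified comparison. A reader of the results could not tell whether the emphasised visit was chosen before or after the data were seen.

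**Working it through.** **1. The plan's own sample size.** With the normal formula, two-sided 0.05, 80% power and d = 0.91:

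n per arm = 2 × (1.960 + 0.842)² / 0.91² = 2 × 7.85 / 0.828 ≈ 18.96, so 19.

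Allowing for dropout: 38 / (1 − 0.20) = 47.5, so 48. The stated figures reproduce, as the size for one comparison at 0.05. The exact t-test gives 20 per arm. Exact power is 77.9% at 19 per arm and 87.0% at 24 per arm.

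**2. False-positive rate if any one of three visits suffices.** Both the nominal 5% and the rates below count errors in either direction.

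Independent tests: 1 − 0.95³ = 1 − 0.857 = 14.3%.

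Correlated tests, by simulation of three equally correlated normal test statistics (2,000,000 draws each):

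| Correlation between test statistics (assumed) | Chance of at least one p < 0.05 under no difference |
|---|---|
| 0 | 14.3% |
| 0.3 | 13.6% |
| 0.5 | 12.5% |
| 0.7 | 10.9% |
| 0.8 | 9.9% |
| 0.9 | 8.4% |
| 0.95 | 7.4% |

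The rate falls to 5% only when the three tests are perfectly correlated.

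**3. Which correlation is relevant.** The outcome is change from baseline, so what matters is the correlation between change scores, not between raw VAS values. Assume equal variances σ² at all visits and the same correlation ρ between every pair of visits. Then:

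- variance of one change score = 2σ²(1 − ρ)
- covariance of two change scores sharing a baseline = σ²(ρ − ρ − ρ + 1) = σ²(1 − ρ)
- correlation = σ²(1 − ρ) / 2σ²(1 − ρ) = 0.5, whatever ρ is.

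Simulated t-tests on change scores at 19 and 24 per arm, with ρ from 0.3 to 0.8, gave 12.5% to 12.8%, in line with the table's 0.5 row. Unequal visit correlations would move the figure within the table.

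**4. What an alpha split would cost.** Bonferroni uses 0.05 / 3 = 0.0167 per visit. Exact t-test power at d = 0.91:

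| Patients per arm | alpha 0.05 | alpha 0.0167 |
|---|---|---|
| 19 (after the full 20% dropout) | 78% | 62% |
| 24 (no dropout) | 87% | 75% |

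Restoring 80% power at 0.0167 needs 26 per arm by the normal formula (52 / 0.8 = 65, or 66 in equal arms). The exact t-test needs 27 per arm (54 / 0.8 = 67.5, so 68).

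**The case against.** **No one-visit rule is written.** A reader might infer that the protocol gives the trial three chances to succeed. It does not say so. A rule that all three visits must be significant would remove the inflation. This stands, and it limits the point: the defect is a missing decision rule, and the inflated rate applies only under a reading the text leaves open.

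**The visits have different roles.** Table 1 labels week 2 as mid-intervention and week 4 as post-intervention, and the Study design overview assigns the follow-up VAS to sustained effect. That suggests week 4 is the natural main visit, but no section makes it decisive, and the Primary outcome section ranks all three alike.

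**The analysis plan may settle it.** A protocol article can leave multiplicity to a statistical analysis plan that is not shown. Here, though, the article itself fixes three primary visits and 0.05 for every analysis, so a plan that adjusted would contradict the published text.

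**The rate is not a known number.** A reader might want to quote one figure, such as 11–12%. The article gives no correlation between VAS visits, so only a range under stated assumptions can be supported.

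**The same threshold covers the secondary outcomes.** It does, but unadjusted secondary tests are common and their handling is often left to the analysis plan. They form no part of this finding.

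**Conclusion.** The point holds as a flaw in what the article fixes: three co-equal primary visits, separate two-group tests at an unadjusted 0.05, and no rule for combining them. If one significant visit may carry the claim, the false-positive rate is about 12.5% at a correlation of 0.5 between test statistics, and about 7% to 14% over correlations from 0.95 to 0. The 0.5 rests on equal variances and equal visit correlations, and the range rests on assumed correlations throughout. That the rate exceeds 5% does not depend on the value chosen, short of perfect correlation. The stronger statement, that the trial as designed has one definite inflated error rate, is not supported. The 48 patients are correctly derived for a single comparison, but the article does not say which one. This should be corrected, because the error rate of the main claim depends on it.

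**What to change.** Before unblinding:

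1. **Name one primary comparison:** the between-arm difference in VAS change from baseline at a single visit, two-sided 0.05. Week 4, the end of treatment, is a reasonable choice. The sponsor should choose the visit to which d = 0.91 refers, and say so in the Sample size calculation.
2. **Place the other two visits.** Either make them secondary, or list them in a stated order and test each at two-sided 0.05 only if every comparison before it was significant. The fixed sequence holds the overall rate at 5%.
3. **Narrow the threshold sentence in Data analysis.** Limit the confirmatory 0.05 to the primary comparison, or to the sequence if one is used. Label all other p-values as unadjusted and supportive.
4. **Align the abstract, the Primary outcome section and Tables 1 and 2.**

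This needs no extra patients, visits or data. It does mean that an effect seen only at another visit cannot be claimed as the primary result. The article describes randomization and treatment partly in the past tense, so enrolment may have begun. If it has, record the change as a dated amendment with its reason and a statement that no unblinded results had been seen. Keeping three co-equal visits with Bonferroni is valid but costs the power shown above, or about 66 to 68 patients in place of 48.
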